### Intervention description {11a}

Participants will be divided into two main groups: group 1 (HILT) and group 2 (sham HILT). Within each group, there will be two subgroups for men and women, determined through a simple randomization process and stratification by sex, utilizing the research randomizer program [25]. his allows the researchers to analyze the outcomes of interest by group and by subgroup. This study recognizes the superior benefits of passive stretching for flexibility improvement, post-exercise recovery, and range of motion limitations, especially in CNNP patients [26–29]. Both groups will receive as a base treatment a bilateral passive stretching exercise plan of the upper trapezius muscle, levator scapulae, and scalenes in 3 series for 30 s [27, 28]. Treatments will be performed twice a week for 4 weeks with 3 assessments: before treatment (T0), at the end of treatment (T1), and 12 weeks after treatment (follow-up) (T2).

#### High-intensity laser application (HILT) — experimental group

HILT will be applied on the map of 12 points evaluated with algometry using the spot technique, while the upper trapezius muscle belly will be treated with a scanning technique, covering an area of 100 cm^2^ [24, 30]. The perimeter of the trapezium treatment area will be delimited using a 5 × 20-cm transparent lens that will be placed in the center of the area limited by the spinous process of C7 and the acromion (Fig. 1).

**Fig. 1 Fig1:**
[figure not shown]
Delimitation of the trapezius treatment area

For the laser therapy application, the 12W BTL-6000 equipment will be used. The energy dose proposed by Dundar et al. that combines the HILT scanning and spot techniques [30] is as follows: An energy of 10 J will be delivered per point (60 J in total for each side), and 1000 J of manual scanning for 100 cm^2^ of the upper portion will be divided into two phases of 500 J (a total of 1000 J for each side), delivering a total of 1060 J for each side of the body in each treatment. Table 1 shows the technical specifications of the laser equipment and the treatment parameters. The treatment protocol will be carried out in three phases:*Phase 1 (scanning)*: continuous mode, peak power of 12 W for 42 s, delivering a total energy of 500 J in the upper trapezius muscle belly (area of 100 cm^2^).*Phase 2 (spot technique)*: pulsed mode, duty cycle of 25%, average power of 1 W for 10 s, delivering 10 J per point, completing a total of 60 J for each side.*Phase 3 (scanning)*: continuous mode, peak power of 6 W for 83 s, delivering a total energy of 500 J in the upper trapezius muscle belly (area of 100 cm^2^).

**Table 1 Tab1:** High-intensity laser therapy characteristics and parameters

**Laser technique specifications**	
Wavelength	1.064 nm
Output power	12 W
Beam divergency	35°
Emission mode	Continuous or pulsed
Frequency (only for pulsed mode)	1–100 Hz (fixed duty cycle 25%)
Spacer	30 mm
Spot size	3.14 cm^2^
**Laser treatment parameters for each side**	
Peak power (W)	Phase 1: 12 W Phase 2: 4 W Phase 3: 6 W
Emission mode	Phase 1: continuous mode (duty cycle 100%) Phase 2: pulsed mode at 100 Hz (duty cycle 25%) Phase 3: continuous mode (duty cycle 100%)
Mean power (W)	Phase 1: 12 W Phase 2: 1 W per point Phase 3: 6 W
Application technique	Phase 1: contact, manual scan for 100 cm^2^ Phase 2: contact, punctual technique for 6 points per side Phase 3: contact, manual scan for 100 cm^2^
Application angle	90°, perpendicular to the skin
Power density (W/cm^2^)	Phase 1: 0.038 W/cm^2^ Phase 2: 0.31 W/cm^2^ Phase 3: 0.019 W/cm^2^
Treatment time (sec)	Phase 1: 42 s Phase 2: 10 s per point (60 s for 6 points) Phase 3: 83 s
Energy density (J/cm^2^)	Phase 1: 5 J/ cm^2^ Phase 2: 3.1 J/ cm^2^ per point Phase 3: 5 J/c cm^2^
Energy delivered per side (J)	Phase 1: 500 J Phase 2: 60 J Phase 3: 500 J Total per side = 1.060 J

*Abbreviations: cm*^*2*^ square centimeters, *Hz* hertz (cycles per second), *J* joules, *mm* millimeters, *nm* nanometers, *sec* seconds, *W* watts

#### Sham high-intensity laser application (HILT) — control group

For sham HILT intervention, individuals will be treated with the same care as the current intervention group, including dose, therapy time, individual care, and the physical space where the therapy will be performed. The placebo intervention will be performed as a control.

#### Stretching exercises — experimental and control groups

While both active and passive stretching can enhance flexibility, passive stretching tends to yield greater improvements, making it recommended for addressing range of motion restrictions in CNNP [26–29]. As a result, both groups in the study will be subjected to a bilateral passive stretching protocol targeting the upper trapezius, levator scapulae, and scalenes muscles.

The practitioner will stretch the participants’ muscles by taking the neck to the points of maximum tension and holding that position. The stretches will consist of 3 series of 30 s, with an interval of 30 s between series [27, 28]. The exercises will be carried out with the participant in a seated position in a chair with a backrest. Stretching exercises will be performed by a physical therapist after the treatment assigned to each group (HILT or sham HILT).

### Criteria for discontinuing or modifying allocated interventions {11b}

There will be no changes in assignments, nor will migration of individuals between groups be allowed. If people discontinue treatment, the analysis will be by “intention to treat,” recording the reasons for leaving the study.

### Strategies to improve adherence to interventions {11c}

To minimize data loss, all participants will be provided with guidance when they sign the informed consent form and commit to attending on the scheduled treatment dates. Participants will receive an appointment card to attend sessions. An evaluator will be responsible for notifying and monitoring the participants on a weekly basis (via telephone contact, WhatsApp, and/or email) and accompanying them during the research.

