### Provisions for post-trial care {30}

During the initial evaluation session, participants will be given a document outlining all the considerations that should be made during the study period. The principal researcher will provide participants with his phone number, the researchers’ email addresses, and contact information about the physical therapy department at Andrés Bello University. The evaluators will keep an electronic record (in Microsoft Excel) of the medications taken during the week. In general, the treatments are safe and do not pose risks for the participants. However, if the individual exhibits any negative effects, they will be referred to the university health center for evaluation and treatment.

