### Implementation {16c}

Four independent physical therapists will work on this study, and each of them will have a specific role. The principal researcher (R1) will oversee participant recruitment, participant registration, randomization, and the random allocation sequence. Moreover, the interventions will be implemented by a researcher (R2) (HILT, sham HILT, and exercise). All evaluations will be performed by a third researcher (R3) (RPI, MPI, PPT, CROM, and ND). The principal researcher will examine and record the data.

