## Assignment of interventions: blinding

### Who will be blinded {17a}

Evaluators will be blinded to the randomization and intervention processes; they will be responsible only for the evaluation procedures and will not receive information about the assignment of individuals to groups. Participants and the principal researcher responsible for the treatment will not be blinded due to the nature of the interventions.

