### Plans to promote participant retention and complete follow-up {18b}

Principal researcher (R1) and an evaluator (R2) will be responsible for notifying and monitoring the participants on a weekly basis (via telephone contact, WhatsApp, and/or email) and accompanying them during the research.

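### Evaluators are meant to assess only and stay blind, yet they are given weekly participant contact and the medication log, and the contact evaluator carries the treating researcher's code

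*Protocol article*

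**What the plan says.** Section {17a} of the protocol article sets the rule for evaluators: "Evaluators will be blinded to the randomization and intervention processes; they will be responsible only for the evaluation procedures". They also "will not receive information about the assignment of individuals to groups". The same section adds: "Participants and the principal researcher responsible for the treatment will not be blinded".

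Three other sections give evaluators further work:

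- {11c}, on adherence: "An evaluator will be responsible for notifying and monitoring the participants on a weekly basis". The contact is by telephone, WhatsApp or email, and the evaluator also accompanies participants through the study.
- {18b}, on retention: "Principal researcher (R1) and an evaluator (R2) will be responsible for notifying and monitoring the participants on a weekly basis".
- {30}, on post-trial care: "The evaluators will keep an electronic record (in Microsoft Excel) of the medications taken during the week".

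Section {16c} defines the codes. R1 is the principal researcher, who recruits and randomizes. R2 delivers HILT, sham HILT and the exercises. R3 performs every evaluation. Section {12} instead describes two evaluators, one for pressure pain threshold and pain intensity and one for range of motion and disability. Section {8} calls the patient, as well as the evaluator, blinded.

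**The concern.** Among participants and the staff who meet them, evaluators are the only people whose blinding is stated without contradiction: the Abstract, {8} and {17a} agree on it. Pain intensity is reported to the evaluator, and a pressure threshold depends partly on how the evaluator applies the algometer, so this blinding protects the main outcomes.

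Regular contact over several weeks with people who may know their arm is an avoidable way to lose that protection. The protocol states no safeguard against it. Section {17b} forbids evaluators to break the blind, but does not deal with a participant who mentions the treatment. If the code R2 in {18b} were correct, an evaluator would also be the person who knows every allocation, because under {16b} whoever administers treatment opens the envelopes.

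**Working it through.** No arithmetic applies. The check sets the sections side by side.

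**1. Assessment only, against other duties.** {17a} restricts evaluators to assessment. {11c} and {18b} give an evaluator weekly contact, and {30} gives the evaluators the medication record. These statements cannot all stand as written.

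**2. Who the contact evaluator is.** There are four ways to read the code in {18b}:

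| Reading of the evaluator coded R2 in {18b} | Consequence |
|---|---|
| The therapist R2 of {16c}; the word evaluator is the error | Under {18b}, contact is by two unblinded non-assessors, which is harmless to assessor blinding; {11c} still assigns it to an evaluator |
| Slip for R3 of {16c} | The assessor of all outcomes, including pain and pressure threshold, makes the weekly contacts |
| Evaluator 2 of {12} | The assessor of range of motion and disability makes the contacts; the main outcomes are scored by someone else |
| Literal: R2 both treats and evaluates | Contradicts {17a}, and contradicts {16c}, which gives all evaluations to R3 |

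The document does not decide among these. Each needs a correction somewhere, and the second and third place a blinded assessor in weekly contact.

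**3. Whether participants can disclose their arm.** {17a} says they are not blinded; {8} says they are. {6b} and the description of the sham intervention fit {8}, since the sham matches active treatment in time, care and setting. If {17a} governs, each contact is a chance of disclosure. If {8} governs, participants have at most a guess to disclose.

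**4. Whether the extra duties reveal allocation.** A reminder or a list of medicines taken does not show the arm. The risk lies in the conversation, and it exists only where an assessor makes the contact and the participant knows or believes something about the arm.

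**5. Who could take over the contact.** R1 is already named in {18b}. R1 holds the randomization sequence under {16b} and {16c} and performs no outcome assessment under {16c}, so contact by R1 cannot unblind an assessor.

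**The case against.** **The conflict may be only one of labels.** {16c} gives all evaluations to R3, so R2 in {18b} could be a misprint. A reader might infer that the therapist who applies the laser also scores outcomes. The documents do not support that: it rests on one shared code and runs against {16c} and {17a}. The need to correct the code stands.

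**The contact person may not measure the main outcomes.** A reader might infer that whoever applies the algometer and records pain is also the weekly caller. No section says so. {11c} does not specify which evaluator it means, and under the split in {12} it could be the one who measures range of motion and disability. This limits the point to a possible exposure of the main outcomes.

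**The word only can be read narrowly.** In {17a} it may just contrast assessment with randomization and treatment, and recording medication is a form of data collection. That is fair for the medication record. It is less convincing for weekly contact and accompaniment, which are retention work.

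**If participants know their arm, self-reported pain and disability are exposed to bias whoever makes the calls.** This is correct, and it means that evaluator contact adds less harm than it first appears to. Pressure threshold and range of motion, which depend more on the assessor, remain the clearest places where evaluator blinding matters.

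**Counts and error rates.** It is tempting to multiply 84 participants by 16 weeks (4 of treatment plus 12 of follow-up) and call the product, 1,344, chances of unblinding, or to assume a bias in SD units and convert it to a false-positive rate. Neither sizes this defect. The task is shared with R1, many contacts would be brief reminders, {12} puts follow-up at week 20, and nothing in the document links a reminder to a shift of any given size.

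**Conclusion.** The point holds as an inconsistency of roles with a plausible consequence for blinding. {17a} is incompatible as written with {11c}, {18b} and {30}, and the code R2 conflicts between {16c} and {18b}. An evaluator in weekly contact could learn a participant's arm before scoring outcomes.

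This rests on two conditions that the document leaves open: that the contact is in fact an outcome assessor, and that participants are unblinded, as {17a} says and {8} denies. The size of any bias cannot be derived from the document. The text does not show that any evaluator will be unblinded, that the therapist assesses outcomes, or that the pain assessor makes the calls. A correction is worthwhile because it is cheap and restores what {17a} already promises.

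**What to change.** - In {11c} and {18b}, assign weekly contact and accompaniment to R1 or to another person who assesses no outcomes.
- Correct the description of R2 as an evaluator in {18b}, and reconcile the codes R2 and R3 and the number of evaluators across {12}, {16c} and {18b}.
- State that evaluators meet participants only at the assessment visits (baseline, end of treatment and 12-week follow-up), and that participants are told not to mention their treatment there.
- Reconcile {8} and {17a} on whether participants are blinded.
- In {30}, either keep the medication record with the evaluators and take it at the assessment visits, or move it to R1 with a fixed script.

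The cost is some added workload for R1, with no extra staff, visits or participants. Moving the medication record has a further drawback: medication use would be recorded by someone who knows the allocation. That matters because {10} makes use of analgesics during the study an exclusion criterion, so the script should be identical for both arms. Leaving the record with evaluators at assessment visits avoids this, but participants must then recall over a longer period than a week.

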### Relevant concomitant care permitted or prohibited during the trial {11d}

During the experiment, concurrent treatments such as chronic diabetes, hypertension, anxiolytics, and antidepressant drugs will be accepted. Throughout the course of the trial, participants will not be allowed to start any other interventions or medications, especially on the days that the evaluations and treatments are carried out.

### Provisions for post-trial care {30}

During the initial evaluation session, participants will be given a document outlining all the considerations that should be made during the study period. The principal researcher will provide participants with his phone number, the researchers’ email addresses, and contact information about the physical therapy department at Andrés Bello University. The evaluators will keep an electronic record (in Microsoft Excel) of the medications taken during the week. In general, the treatments are safe and do not pose risks for the participants. However, if the individual exhibits any negative effects, they will be referred to the university health center for evaluation and treatment.

### Outcomes {12}

The main outcomes will be the changes in pain intensity at rest (RPI), pain intensity at movement when performing active cervical movements in the sagittal (flexion–extension), coronal planes (neck right and left side bending) and transverse plane (right and left rotation) (MPI), and pressure pain threshold obtained as a mean of six points of the cervical spine and shoulder region according to the protocol of Rampazo et al. (Fig. 3) (PPT). Secondary outcome measures, on the other hand, will include differences in cervical range of motion (CROM) and neck disability (ND) after the HILT application in participants with chronic nonspecific NP. The evaluations will be carried out by two independent evaluators: evaluator 1 (PPT and PI) and evaluator 2 (CROM and ND). PPT will be evaluated with algometry at six established bilateral points [24] (Fig. 3), RPI and MPI with numeric pain rating scale (NPRS) [31], cervical ROM with an inclinometer (CROM device) [32–34], and neck disability (ND) through the neck disability index (NDI) [35, 36]. The evaluations of the outcome measures of interest will be carried out in three instances: pretreatment (T0: baseline), the fourth week (T2: the 8th HILT session, end of treatment), and week 20 (T3: 12 weeks post-treatment or follow-up) (Fig. 2).

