**Methods:**

This is a 2-arm, randomized, placebo-controlled trial with blinded evaluators. The research will be carried out in the laboratory of physical agents at the Andrés Bello University, Campus Casona de las Condes. Eligible participants include the entire internal and external community associated with Andrés Bello University suffering from chronic non-specific NP. Participants will be stratified by sex (4 subgroups) and randomized into 2 study groups: group 1 (HILT and stretching exercises) and group 2 (sham HILT and stretching exercises). Treatments will be performed twice a week for 4 weeks with 3 assessments: before treatment (T0), at the end of treatment (T1), and 12 weeks after treatment (follow-up) (T2). The main outcomes will be pain intensity at rest, pain intensity at movement (active cervical movements: flexion, extension, right and left side bending, and right and left rotation), and pain pressure threshold (average obtained for six evaluation points). Secondary outcome measures will include neck range of motion in the sagittal, coronal, and transverse planes and neck disability.

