### Objectives {7}

The main purpose of the research is to investigate whether pain intensity will decrease after HILT treatment compared with sham HILT after treatment and with a 3-month follow-up. Additionally, secondary outcomes such as changes in pain pressure threshold, active cervical range of motion (flexion, extension, left- and right-side bending, and left and right rotation), and cervical disability will be evaluated. The hypothesis of the study is that HILT will lead to greater pain intensity improvement than conventional treatment. The purpose of this article is to describe the methods and statistical analysis of this study so that this information can be made public.

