#### Pain intensity at rest and on movement (RPI and MPI)

Pain intensity will be evaluated through the numerical pain scale (NPRS: intra-rater reliability; intraclass correlation coefficient, ICC = 0.76 (95% CI: 0.51,0.87) [29]. The RPI will equal the magnitude of neck pain reported by the participants at rest, while the MPI will be represented as the magnitude of pain reported by the participants when performing active cervical movements in the sagittal (flexion–extension), coronal (neck right and left side bending), and transverse planes (right and left rotation) [31]. The paint intensity with NPRS will be assessed for each movement using a single attempt (a total of six movements). The RPI and MPI exams will be performed by the participant in a seated position, keeping the back straight and supported on a backrest. The RPI and MPI values will be recorded on a Microsoft Excel® spreadsheet.

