## Statistical methods

### Statistical methods for primary and secondary outcomes {20a}

The descriptive statistics for the variables RPI, MPI, PPT, CROM, and ND will be used as analysis measures: averages and standard deviation (*x*, SD), median and interquartile range (mean, IQR), depending on the distribution of the data (test of Kolmogorov–Smirnov normality). From these data, a table will be constructed with the demographic data of the participants by group. The secondary variables sex and body mass index (BMI) will be presented with frequencies and averages or medians, respectively, according to the analysis of the normality of the data. For the inferential statistical analysis of the outcome measures, the Kolmogorov–Smirnov normality test and the Bartlet test will be used to determine the distribution of the variables PPT, RPI, MPI, CROM, and ND, and the corresponding homoscedasticity of the variances obtained for these variables in the evaluations (T0, T1, and T2). According to the results, parametric or non-parametric tests will be selected: the changes in the measurement variables within and between groups will be analyzed with the two-factor ANOVA or the Kruskal–Wallis test, depending on the distribution of the data. Subsequently, a post hoc analysis will be carried out with the Tukey or Bonferroni test, depending on the statistical differences. The significance level for all statistical tests will be set at 0.05. Data will be analyzed using IBM Statistical Package for the Social Sciences (SPSS) software (version 26; SPSS Inc.; Chicago, IL) by an investigator who is blind to group assignment.

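### Three main outcomes, one of them also called secondary, are tested at 0.05 with no primary time point and no rule across outcomes, so the chance of a false positive main result exceeds 5% if any one of them counts as success

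*Protocol article*

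**What the plan says.** Outcomes {12} lists the main outcomes as "The main outcomes will be the changes in pain intensity at rest (RPI), pain intensity at movement when performing active cervical movements" (MPI), "and pressure pain threshold obtained as a mean of six points of the cervical spine and shoulder region". The abstract's Methods paragraph lists the same three and ends with "and pain pressure threshold (average obtained for six evaluation points".

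Objectives {7} differs. The main purpose there is to "investigate whether pain intensity will decrease after HILT treatment compared with sham HILT after treatment and with a 3-month follow-up", and PPT appears under "secondary outcomes such as changes in pain pressure threshold, active cervical range of motion".

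The section on pain intensity at rest and on movement says that pain is "assessed for each movement using a single attempt (a total of six movements"). It gives no rule for combining the six ratings into one MPI value, whereas PPT is explicitly averaged.

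Outcomes are assessed at baseline, at the end of treatment (week 4) and at follow-up (week 20). Neither later visit is named as primary. The visit labels also disagree: T2 is the follow-up in the abstract but the end of treatment in Outcomes {12}.

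Statistical methods {20a} plans a two-factor ANOVA or a Kruskal–Wallis test for RPI, MPI, PPT, CROM and ND, then Tukey or Bonferroni as a post hoc step. It adds: "The significance level for all statistical tests will be set at 0.05". Sample size {14} is calculated for one difference in mean pain intensity with an error of 5%.

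**The concern.** The protocol does not say which result decides whether HILT works. Three outcomes share main status, one of them has two labels, two visits carry equal weight, and nothing says whether one main outcome or all of them must be positive. The only multiplicity step sits inside the analysis of each outcome and does nothing across outcomes.

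The trial could therefore be reported as positive on whichever main outcome and visit reaches 0.05. PPT could be treated as main or secondary after the data are seen without departing from the text. The 5% error rate assumed in the sample size would not apply to the trial's conclusion.

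**Working it through.** **The plan's own figure.** Sample size {14} gives d = 0.6, power 0.80, error 5% and 72 participants (36 per group), raised to 84. A two-sample t-test (noncentral t) gives 36 per group, 72 in total, if one-sided, and 45 per group, 90 in total, if two-sided. So 72 reproduces for one comparison at one-sided 0.05; the protocol does not state sidedness. Adding 15% gives 36 × 1.15 = 41.4, rounded up to 42 per group, or 84. Nothing in the calculation allows for more than one main test.

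**Inputs for the error rate.**
- Main outcomes: 3 (abstract; Outcomes {12}).
- Ratings behind MPI: 6 (pain intensity section). Separate measures if MPI is not summarised: RPI + 6 MPI + PPT = 8.
- Visits after baseline: 2 (Outcomes {12}).
- Level per test: 0.05 (Statistical methods {20a}).
- Correlation between tests: not given; assumed common values from 0 to 0.9.

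**Formula.** With no treatment effect and k independent tests, the chance of at least one significant result is 1 − 0.95^k. For correlated tests, 400,000 draws from a multivariate normal distribution were used, counting any two-sided result at 0.05.

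- k = 3: 1 − 0.95³ = 14.3%
- k = 3 × 2 = 6: 1 − 0.95⁶ = 26.5%
- k = 8 × 2 = 16: 1 − 0.95¹⁶ = 56.0%

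| Reading of the plan | Tests | Corr. 0 | 0.5 | 0.7 | 0.9 |
|---|---|---|---|---|---|
| MPI as one score, visits protected within outcome | 3 | 14.3% | 12.5% | 10.9% | 8.4% |
| MPI as one score, both visits unadjusted | 6 | 26.5% | 20.7% | 16.4% | 10.8% |
| Six separate MPI tests, both visits unadjusted (worst case) | 16 | 56.0% | 37.3% | 26.4% | 14.6% |

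**Less uniform correlations.** Assume 0.5–0.8 among pain ratings, 0.2 between PPT and pain, and 0.5–0.7 between visits. The three rows become 12–14%, 20–23% and 30–44%. With an explicit Bonferroni split over the two visits, three outcomes give 11–13% and eight measures 17–26%.

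**Dropping PPT.** Following Objectives {7} leaves RPI and MPI: 1 − 0.95² = 9.75% if independent, with MPI as one score and one test per outcome.

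**Price of a plain Bonferroni split.** At 42 per group, d = 0.6, two-sided, power is 78% at 0.05, 62% at 0.05/3 = 0.0167 and 52% at 0.05/6 = 0.0083.

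**The case against.** **Post hoc protection.** The Tukey or Bonferroni step may protect the two visits within each outcome, so counting the visits as unadjusted tests is only one reading. This stands, and it is why the three-test row is the base case. The protection is not certain: the two-factor ANOVA gives both a group and a group-by-time test, and Kruskal–Wallis cannot model the two factors jointly. In neither case does the step reach across outcomes.

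**MPI as one variable.** Statistical methods {20a} lists MPI as a single variable. A reader might infer from the six ratings that sixteen main tests are planned and that the error rate is 56%. The protocol does not say that. It only leaves the score undefined, and independence among six ratings from one person in one sitting is implausible. The sixteen-test figures are a worst case.

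**Success rule.** The inflation arises only if any one positive main outcome counts. If all three had to be positive there would be none. The protocol states neither rule, so the condition must be kept in view.

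**Choice of primary.** A reader might infer that the objective and the sample size already single out pain at rest. They do not: both refer to pain intensity without specifying rest or movement, and the Discussion expects effects on PPT and movement pain without mentioning rest. Only the entry criterion, a rest NPRS of 3 or more, points to RPI.

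**Left to an analysis plan.** Scoring detail may well sit in an analysis plan that is not shown. That does not cure the contradictory status of PPT or the unadjusted 0.05, both of which are in the protocol's own text.

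**Conclusion.** The concern holds in this form. The conflict over PPT and the lack of any rule across the main outcomes can be read directly from the text. The size of the inflation is conditional: it assumes that one significant main outcome would count as success, and it uses correlations that the protocol does not supply.

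On the base reading the false positive rate is about 8–14% (correlation 0.9 to 0), roughly 1.7 to 2.9 times the nominal 5%. It is 21–26% (correlation 0.5 to 0) if both visits are tested unadjusted, and 26–56% (correlation 0.7 to 0) in the worst case. A flat statement that the rate is several times 5% would go beyond the documents. The double label of PPT adds no error by itself, but it leaves the main family open to choice after the data are seen.

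**What to change.** Before unblinding:

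1. Name one primary pain-intensity outcome at one time point, identically in the abstract, Objectives {7} and Outcomes {12}, and identify the visit by week because the T labels conflict. RPI at the end of treatment is a natural candidate given the entry criterion, but the choice is the investigators'.
2. Define MPI as the mean of the six movement ratings.
3. Reconcile the status of PPT across the same three places.
4. In Statistical methods {20a}, test the second time point and any remaining main outcomes in a prespecified fixed order, or by Holm, at an overall 0.05. Report all other outcomes with confidence intervals and no confirmatory claim.

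A fixed order keeps the full 0.05 for the first test and so avoids the power loss of a Bonferroni split shown above.

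The cost is a substantive protocol and registry amendment, since the trial was registered in January 2023 and recruitment was planned from April 2023. The registry's own primary outcome is not in the documents and should be checked at the same time. The other main outcomes lose independent confirmatory status.

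### The Outcomes section puts follow-up at week 20 and also at 12 weeks after a treatment ending in week 4; these differ by four weeks, and its visit labels depart from the rest of the article

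*Protocol article*

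**What the plan says.** The Intervention description {11a} gives the length of treatment: "Treatments will be performed twice a week for 4 weeks with 3 assessments". It places the two later assessments "at the end of treatment (T1), and 12 weeks after treatment (follow-up) (T2". The Methods paragraph of the Abstract gives the same schedule and labels: "before treatment (T0), at the end of treatment (T1), and 12 weeks after treatment (follow-up) (T2". The Objectives {7} make the follow-up part of the main question, comparing pain intensity after treatment and "with a 3-month follow-up".

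Outcomes {12} is the section that fixes when each outcome is measured. It dates end of treatment and follow-up as "the fourth week (T2: the 8th HILT session, end of treatment), and week 20 (T3: 12 weeks post-treatment or follow-up". It calls baseline T0 and has no T1.

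The Fig. 2 caption, whose figure is not shown, expands t1 as the post-treatment evaluation and t2 as the follow-up. The Statistical methods {20a} refer to distribution and variance checks "in the evaluations (T0, T1, and T2", without saying which visit each label denotes.

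**The concern.** A single sentence gives the follow-up visit both a study week and an interval since treatment, and the two disagree. The sentence governs pain at rest, pain on movement and pressure pain threshold, as well as range of motion and disability. The follow-up comparison asks whether any benefit lasts, so the time since the last session is part of what is being estimated.

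Two things are at stake. If the visit is booked by week number, the finding presented as 12-week or three-month durability would in fact describe 16 weeks. If some visits are booked by week number and others by interval, the time since treatment would differ between participants by up to four weeks. That adds noise, and it would bias the comparison only if the timing differed between arms.

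The labels are a second, smaller inconsistency in the same sentence. T2 means end of treatment there and follow-up in the other places that define it.

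**Working it through.** **Inputs**

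- Treatment: two sessions a week for 4 weeks (Abstract; Intervention description {11a}).
- End of treatment: fourth week, eighth session (Outcomes {12}).
- Follow-up: 12 weeks after treatment (Abstract; Intervention description; Outcomes), or 3 months (Objectives {7}).
- Follow-up study week: 20 (Outcomes only).

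**Step 1. Is the end of treatment consistent?** 2 sessions per week × 4 weeks = 8 sessions. The eighth session in week 4 agrees with the rest of the article.

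**Step 2. Can the stated week 20 be reproduced?** Follow-up week = end-of-treatment week + interval.

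- With 12 weeks: 4 + 12 = week 16, not 20.
- With 3 calendar months: 3 × 365.25 / 12 / 7 = 13.04 weeks, and 4 + 13.04 = 17.04, about week 17.
- Working back from week 20: 20 − 4 = 16 weeks after treatment, not 12.
- End of treatment needed for week 20 to be right: 20 − 12 = week 8. At two sessions a week that would be 2 × 8 = 16 sessions, whereas the article has 8.

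No variant returns week 20. The discrepancy is 20 − 16 = 4 weeks, and 4 / 12 = 33% of the stated interval.

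**Step 3. Could the time origin explain it?** Week 4 and week 20 stand in one list on one count. Starting the count at enrolment instead of the first session would move both numbers together and leave the gap at 16 weeks. Reading the fourth week as an ordinal week (between 3 and 4 weeks elapsed) puts the visit at 15 to 16 elapsed weeks, which is still not 20.

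**Step 4. Labels side by side**

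| Place | End of treatment | Follow-up |
|---|---|---|
| Abstract, Methods | T1 | T2 |
| Intervention description {11a} | T1 | T2 |
| Fig. 2 caption | t1 | t2 |
| Outcomes {12} | T2 | T3 |
| Statistical methods {20a} | not defined; lists T0, T1, T2 | not defined; lists T0, T1, T2 |

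Only Outcomes departs from the scheme. The list in Statistical methods has no T3, so it fits the scheme used in the other places.

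**The case against.** The best defence is that this is an isolated slip. Week 20 occurs once, next to its own gloss of 12 weeks, and the interval is repeated in the Abstract and the Intervention description and supported by the Objectives. A careful reader can tell which figure is the odd one out. That argument stands as far as it identifies the likely intention. It does not remove the error, because the wrong figure sits in the section that staff would consult to schedule the visit.

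A reader might infer more than the article supports, in four ways.

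- **Mislabelled data.** One might conclude that end-of-treatment values would be analysed as follow-up. The Outcomes scheme has no T1, so data labelled that way would leave T1 empty and T3 unused in a T0/T1/T2 analysis, and the fault would show. Outcomes also describes each visit in words. A silent mix-up is unlikely.
- **Mixed scheduling as a certainty.** Nothing says that some staff will book by week and others by interval. This is a single-laboratory trial with few evaluators (one in Implementation {16c}, two in Outcomes). If one timing is used throughout, the arms remain comparable and only the reported duration is wrong.
- **All 84 participants affected.** That is an upper bound. It assumes nobody is lost to follow-up, although the Sample size section {14} allows 15% for losses.
- **A faulty figure schedule.** Fig. 2 cannot be seen, and its caption already uses t1 and t2 in the usual sense. It needs checking and is not known to be wrong.

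The defence is also right that the sample size rests on pain differences after treatment, and that the Discussion states its expected benefits at the end of treatment. Neither depends on the follow-up week.

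**Conclusion.** Outcomes {12} is wrong as written: a follow-up at week 20 cannot be 12 weeks after a treatment that ends in week 4. The two statements differ by four weeks, 33% of the 12-week interval, and they concern the follow-up measurement of every main and secondary outcome. Because the Objectives include follow-up in the main question, this is more than a clerical matter.

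The arithmetic needs only the article's own figures and the natural reading that both week numbers in the sentence share one origin. The consequence is conditional: the reported duration is wrong if visits are booked by week number, and timing is uneven between participants if both readings are used. The label mismatch is real but is a matter of clarity. The sample size and the end-of-treatment comparison are unaffected.

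**What to change.** 1. State one follow-up time, anchored on the last treatment session, and use it everywhere. The Abstract, Objectives and Intervention description support 12 weeks after the last session, which is week 16 from the start of treatment. On that reading, replace week 20 in Outcomes {12}.
2. If week 20 was intended, change the interval to 16 weeks in the Abstract, Objectives {7}, Intervention description {11a} and Outcomes {12}.
3. Relabel the visits in Outcomes as T0, T1 and T2, with T1 as end of treatment and T2 as follow-up.
4. Check that the schedule in Fig. 2 shows the same follow-up week. Its caption labels already agree.
5. If any follow-up visits have already taken place, say which timing was used and report the actual interval since the last session by arm.

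The first four items are corrections of wording and a check of one figure. The fifth needs only the session and visit dates. No visits are added and the sample size does not change.
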